##### Implementation study design

Once integrated, the new findings will be mapped to the TDF to enable a comprehensive, targeted theory-informed approach to the development of the implementation strategy [26]. The TDF is used to identify determinants of behaviour and provide comprehensive and systematic approaches to intervention implementation [26]. The mapped TDF domains will be integrated into the BCW, through linking to intervention function(s). The BCW is a validated series of tools for developing behaviour change interventions and is shown to improve the sustained success of clinical interventions [27]. Intervention functions form part of the BCW and are designed to influence behaviour by addressing capability, opportunity, and motivation [27]. If items cross multiple TDF domains and/or intervention functions, the research team will resolve this through a discussion, led by a senior member of the research team with extensive experience in the use of the TDF and behaviour change theories (lead author). The final implementation strategy will be refined using behaviour change techniques taxonomy and the APEASE criteria (Acceptability, Practicability, Effectiveness, Affordability, Spill-over effects, Equity) [28].

### Phase 3: Implementation evaluation of HIRAID® Inpatient

#### Study design

In Phase 3, the HIRAID® Inpatient framework will be implemented using a Type II effectiveness-implementation hybrid design [29], including a SW-cRCT [30]. The hybrid approach allows testing of the implementation strategy at the same time as observing the outcomes of the intervention [29, 30]. Four clusters will be progressed through three sequential phases: control, intervention transition and post-intervention, with a staggered rollout and a 1:1 allocation ratio, with most data collected from each defined population as outlined in Table 4. The trial is structured within a superiority framework, aiming to demonstrate improved outcomes compared to usual care.

Each participating hospital ward (cluster) will begin in the control phase, representing a period of routine or usual care before the scheduled implementation of the HIRAID® Inpatient framework. During this phase, baseline data and behavioural diagnostics will be collected to serve as the comparator for the intervention. Rather than using a separate, concurrent control group, this SW-cRCT uses each cluster as its own control. Data gathered during the pre-intervention phase will be directly compared with data collected post-implementation. This design enables evaluation of the intervention against established, real-world clinical practice. The HIRAID® Inpatient intervention will then be implemented over a three-month period (Intervention Transition), followed by an intervention data collection period, lasting between 3 and 12 months, depending on the cluster (Fig. 3).

**Fig. 3 Fig3:**
[figure not shown]
The stepped-wedge cluster randomised controlled trial design for the implementation of HIRAID® Inpatient across four clusters. Each sequence comprises a 3- to 12-month baseline control condition, a 3-month intervention transition period, and a 3- to 12-month intervention exposure condition

##### Hypotheses

The evaluation of the intervention will test the seven hypotheses listed in Table 1.

**Table 1 Tab1:** List of the seven primary hypotheses to be tested throughout the implementation and evaluation of HIRAID® Inpatient

Hypothesis	Implementation of HIRAID® Inpatient will result in a…
H_1_	…20% reduction in rapid response team activation due to preventable patient deterioration
H_2_	…10% reduction in Hospital Acquired Complications (HAC03 and HAC06)
H_3_	…20% reduction in events causing patient harm or near miss
H_4_	…10% improvement in experience of care reported by patient or carer
H_5_	…10% increase in quality of nurse communication and handover
H_6_	…healthcare resource use and cost estimates that will lead to favourable cost-effectiveness estimates
H_7_	…high fidelity (80%) implementation

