#### Study setting

To ensure geographically and clinically diverse settings, the study will take place in three local health districts in two states, comprising a total of 10 hospitals and 35 wards (total 834 beds) from Illawarra Shoalhaven and Western Sydney Local Health Districts in New South Wales, and Eastern Health in Victoria. The ten hospitals will be nested into one of four clusters based on geography and clinical governance to mitigate the risk of contamination. Collectively the study wards manage 4050 patient admissions per month and employ 1259 nurses (Table 2). These hospitals were selected as they admit acutely unwell patients directly from the ED—the patients most at risk for adverse events [4].

**Table 2 Tab2:** Profiles of the ten participating hospitals, including description, hospital acquired infections (per 1000), the annual number of admissions, and ward type

Cluster	Health Service data for 2023		Study ward data for 2023	
	Description	HAI:1000	Admits per year	Ward type
1. Illawarra Shoalhaven North, NSW (Wollongong hospital—6 wards)	Regional: 684 km^2^, Pop: 214,000 +	3.22	11,400	Aged Care, Gastroenterology, General Medicine, Renal, Respiratory, Surgical
2. Illawarra Shoalhaven South, NSW (Shellharbour Hospital—4 wards; Shoalhaven Hospital—4 wards; Milton/Ulladulla Hospital—1 ward)	Rural Regional: 4708 km^2^, Pop: 185,000 +	2.34	12,861	Aged Care, General Medicine, Surgical
3. Western Sydney, NSW (Westmead Hospital—5 wards; Blacktown/Mount Druitt Hospital—7 wards; Auburn Hospital—1 ward)	Metro: 780 km^2^, Pop: 946,000 +	2.35	13,367	Aged Care, Orthopaedics, Cardiology, General Medicine, Haematology, Neurosurgery, Renal, Respiratory, Stroke
4. Eastern Health, VIC (Box Hill Hospital—4 wards; Angliss Hospital—2 wards; Maroondah Hospital—2 wards)	Metro: 2816 km^2^, Pop: 750,000 +	3.33	10,981	General Medicine, Speciality Medicine, Stroke, Surgical (general, plastic surgery and gastric surgery)
10 hospitals	Pop: 2.1 million +		48,609	

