##### Patients with a hospital acquired complication (H_2_)

Rate per 1000 patient days of respiratory (HAC03) and healthcare-associated infections (HAC06), the leading preventable HACs influenced by nursing care. Nationally, HACs are reported by facility per 1000 patient days. In NSW, the study sites are above the state average of 2.17:1000 patient days. The secondary outcomes are hospital resource use and costs (health service perspective) and the rate of all HACs.

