#### Sample size

Sample sizes were calculated for each of the hypotheses. Hypotheses H1, H2, H3, and H6 sample size estimations were conducted collectively, as they will use medical record and cost data from relevant systems for the period of 1 st July 2026 to 1 st December 2027 (Table 4—shaded grey). To maximise the study’s power in detecting true differences, should they exist, the largest sample size estimation is reported and will be used. Sample sizes were calculated with an assumed intra-class correlation of 3%, 5% significance (two-tailed) and 80% power, and applying Woertman’s SW design estimate approach [48]. These sample sizes have been calculated using the most recent data from the study sites and/or previous work by the investigators in this field. To evaluate implementation fidelity HIRAID® facilitators (CNCs/CNEs) employed to assist with education and roll out will be invited to participate in the evaluation of implementation fidelity. The number of staff to be involved in this process will be determined by each LHD.

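### H2 (10% fewer HAC03/HAC06) sits under an 80% power statement, but the protocol's beds, data window and printed infection rates give about 33–45% before any clustering or time adjustment

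*Protocol article*

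**What the plan says.** Table 1 of the Protocol article lists seven primary hypotheses; H2 is a "10% reduction in Hospital Acquired Complications (HAC03 and HAC06"). The outcome paragraph for H2 defines the measure: "Rate per 1000 patient days of respiratory (HAC03) and healthcare-associated infections (HAC06), the leading preventable HACs influenced by nursing care". It adds one external benchmark: "In NSW, the study sites are above the state average of 2.17:1000 patient days".

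The Sample size section states: "Sample sizes were calculated with an assumed intra-class correlation of 3%, 5% significance (two-tailed) and 80% power", using Woertman's stepped-wedge approach. It also says that "Hypotheses H1, H2, H3, and H6 sample size estimations were conducted collectively" and that "the largest sample size estimation is reported and will be used". The 80% therefore applies to H2. The per-hypothesis sample sizes are in Table 4, whose content is not readable in the copy at hand.

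The Study setting section gives the capacity: "10 hospitals and 35 wards (total 834 beds"). Table 2 lists health-service hospital-acquired infections per 1000 for the four clusters: 3.22, 2.34, 2.35 and 3.33. The caption of Fig. 3 gives 3 to 12 months of control, 3 months of transition and 3 to 12 months of intervention. Table 3 shows no H2 data collection during implementation.

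**The concern.** H2 is counted from routine records of everyone on the study wards. Its information is fixed by beds, time and event rate, and recruiting more people cannot raise it. Taking the largest of several sample sizes therefore does not help if the wards cannot generate that many patient days. A 10% relative reduction in an event occurring two or three times per 1000 patient days needs a very large exposure.

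If real power is well below 80%, a true 10% benefit would more likely than not be missed. A reader relying on the stated 80% could then take a non-significant H2 result as evidence against an effect of that size.

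**Working it through.** **The plan's own figure.** The H2 sample size cannot be reproduced, because Table 4 is not visible. What can be checked is whether 80% is attainable with the exposure and rates printed elsewhere.

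**Inputs.** Rate ratio 0.90 (Table 1); two-sided 5% (Sample size); 834 beds (Study setting); rates and admissions from Table 2; 3–12 months per condition (Fig. 3 caption). *Assumptions:* 100% occupancy, with 85% as a check; evenly spaced control periods of 3, 6, 9 and 12 months, mirrored for intervention (6 and 9 inferred); equal beds per cluster; Poisson counts without overdispersion; Table 2 rates per 1000 patient days, used as a proxy for HAC03+HAC06.

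**Exposure.** Mean months per condition = (3 + 6 + 9 + 12)/4 = 7.5. Patient days per condition = 834 × 365 × 7.5/12 = 190,256.

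**Baseline rate.** Admission-weighted mean = (11,400×3.22 + 12,861×2.34 + 13,367×2.35 + 10,981×3.33)/48,609 = 2.77 per 1000.

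**Unadjusted power.** With m control events, power = Φ(|ln 0.9| / √(1/m + 1/(0.9m)) − 1.96), where |ln 0.9| = 0.1054.

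| Rate per 1000 | Control vs intervention events | Power, full wards | Power, 85% occupancy |
|---|---|---|---|
| 2.34 | 445 vs 401 | 33% | 29% |
| 2.77 | 527 vs 474 | 38% | 34% |
| 3.33 | 634 vs 570 | 45% | 39% |

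For the middle row, SE = √(1/527 + 1/474) = 0.0633, 0.1054/0.0633 = 1.665, and Φ(1.665 − 1.96) = 38%.

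**What 80% needs.** Control events = 7.849 × (1 + 1/0.9)/(ln 0.9)² = 1,493. As a rate, 1,493/190,256 = 7.8 per 1000, and 7.8/2.77 = 2.8.

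**Alternatives tried at 2.77 per 1000, full wards.**
- One-sided 5%: 51%.
- All 18 months used, split equally with no transition gap: 45%.
- The 17-month window written in the Sample size section: 37%.
- A Woertman design effect of about 0.65 applied as a plain reduction of total N: about 54% (62% at 3.33). This needs about 694,000 patient days, against 2 × 190,256 = 380,512 available.

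None reaches 80%.

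**Cluster and time effects.** For four sequences by six quarters, with transition cells dropped, the Poisson information matrix at 2.77 per 1000 gives:
- cluster effects only: SE 0.071, power 32%;
- cluster plus linear time: SE 0.146, power 11%;
- cluster plus categorical time: SE 0.153, power 10%.

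Treating cluster as a random effect with small variance raises the time-adjusted figure to at most 15%.

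**Detectable reduction at 80% power (2.77 per 1000).**
- Unadjusted: about 17%; with cluster effects: about 18%.
- Time-adjusted: 1 − exp(−2.80 × 0.146) = 34% (linear) and 1 − exp(−2.80 × 0.153) = 35% (categorical). Allowing for the fewer events at that larger effect moves these to 36% and 38%.

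**The case against.** The strongest objection is that the actual H2 calculation cannot be seen. Table 4 may print its own baseline, and the Sample size section says the inputs came from recent site data or the investigators' earlier work. Table 2 is only a proxy. Its column is labelled infections, so respiratory complications may be extra. It is health-service data rather than study-ward data, and the wards take patients described as high risk. It prints no patient-day denominator. Table 3 also words the outcome as incidence of patient days with a complication, which could be read as counting affected days.

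Much of this stands as a limit on wording. A reader might infer that H2 cannot have 80% power under any inputs; the document does not support that, because no study-ward HAC03+HAC06 rate is visible. A reader might also take 38% as the ceiling; it is the value at the weighted mean, and the top of the range is 45%. Nor is 10–11% the power of the analysis as written: the Statistical methods section names a random cluster effect and confounders but no calendar-time term, and the figure also rests on inferred step lengths.

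The objection does not restore 80%. Whatever Table 4 prints, beds and months cap the patient days. All three NSW values in Table 2 exceed the 2.17 per 1000 patient days quoted under H2, which suggests that the column is on the same scale. Respiratory complications would have to add about 5 per 1000 (7.8 − 2.8) to reach 80%, even unadjusted. Counting several days per complication adds correlated observations, so information would not grow in proportion.

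**Conclusion.** The point holds at the rates the protocol prints: H2's unadjusted power is about 38%, range 33–45% with full wards and 29–39% at 85% occupancy, against a stated 80%. Full occupancy, no overdispersion, no clustering penalty and 18 rather than 17 months all favour the trial. The shortfall in events is a factor of about 2.8.

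The conclusion depends on Table 2 being a fair proxy for the combined study-ward rate; a rate of about 7.8 per 1000 or more would remove it in the unadjusted case. The 10–11% figure is conditional. It applies if calendar time is modelled, as a stepped-wedge analysis normally requires because exposure is confounded with time. The main finding does not need it.

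**What to change.** Recalculate H2 from the combined HAC03+HAC06 rate on the study wards and the patient days achievable from 834 beds over the planned periods. State both inputs beside the result, or point to them if Table 4 already gives them. Say whether the calculation includes a calendar-time term.

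Unless the combined rate is near 7.8 per 1000 or higher, take H2 out of the 80% statement. In its place print the actual power or the detectable reduction: at Table 2 rates, about 17–18% without time adjustment and about 34–38% with it. Report H2 as a rate ratio with a 95% CI, so that a wide interval is not read as absence of effect. If calendar time is modelled, 7.8 per 1000 is not enough: the break-even rate is then about 46 per 1000.

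The cost is one recalculation, some rewording and a less favourable stated figure. Recruitment is scheduled to start in July 2026, and the change needs no alteration to design or data collection.

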#### Study setting

To ensure geographically and clinically diverse settings, the study will take place in three local health districts in two states, comprising a total of 10 hospitals and 35 wards (total 834 beds) from Illawarra Shoalhaven and Western Sydney Local Health Districts in New South Wales, and Eastern Health in Victoria. The ten hospitals will be nested into one of four clusters based on geography and clinical governance to mitigate the risk of contamination. Collectively the study wards manage 4050 patient admissions per month and employ 1259 nurses (Table 2). These hospitals were selected as they admit acutely unwell patients directly from the ED—the patients most at risk for adverse events [4].

**Table 2 Tab2:** Profiles of the ten participating hospitals, including description, hospital acquired infections (per 1000), the annual number of admissions, and ward type

Cluster	Health Service data for 2023		Study ward data for 2023	
	Description	HAI:1000	Admits per year	Ward type
1. Illawarra Shoalhaven North, NSW (Wollongong hospital—6 wards)	Regional: 684 km^2^, Pop: 214,000 +	3.22	11,400	Aged Care, Gastroenterology, General Medicine, Renal, Respiratory, Surgical
2. Illawarra Shoalhaven South, NSW (Shellharbour Hospital—4 wards; Shoalhaven Hospital—4 wards; Milton/Ulladulla Hospital—1 ward)	Rural Regional: 4708 km^2^, Pop: 185,000 +	2.34	12,861	Aged Care, General Medicine, Surgical
3. Western Sydney, NSW (Westmead Hospital—5 wards; Blacktown/Mount Druitt Hospital—7 wards; Auburn Hospital—1 ward)	Metro: 780 km^2^, Pop: 946,000 +	2.35	13,367	Aged Care, Orthopaedics, Cardiology, General Medicine, Haematology, Neurosurgery, Renal, Respiratory, Stroke
4. Eastern Health, VIC (Box Hill Hospital—4 wards; Angliss Hospital—2 wards; Maroondah Hospital—2 wards)	Metro: 2816 km^2^, Pop: 750,000 +	3.33	10,981	General Medicine, Speciality Medicine, Stroke, Surgical (general, plastic surgery and gastric surgery)
10 hospitals	Pop: 2.1 million +		48,609	

#### Participants and eligibility criteria

##### Nursing staff

All permanent and fixed-term employee nursing staff will complete HIRAID® Inpatient training and be invited to participate in the evaluation of the intervention (i.e. surveys on quality of information in handovers and confidence in patient assessment and escalation of care).

##### Medical and allied healthcare staff

Medical and allied healthcare staff employed or contracted by partnering organisations will be eligible to participate in the evaluation of the intervention with no exclusions. Participation will include the completion of staff experience surveys [31], to understand how the intervention improved the quality of nursing communication and handover. Healthcare staff that meet the inclusion criteria will be invited to participate by email invitation for the survey.

##### Inpatients (or their carers) of a study ward

All patients admitted to the ward that meet study inclusion criteria, to evaluate experience, will be provided with a participant information sheet for the study and invited to participate in surveys. Patients are excluded if they are receiving end-of-life care or have moderate–severe cognitive impairment as identified by the treating clinical team.

If under 18, their carer (if over 18) will be approached; otherwise, they will not be invited. We are not targeting paediatric wards; however, there may be outlying paediatric patients admitted to adult inpatient wards.

If the patient is not clinically suitable to approach, (e.g. in significant pain, cognitive impairment), an appropriate carer may be approached. A waiver of consent has been approved for the collection of de-identified inpatient data, which will include medical records, care plans, charts, progress notes, and all associated documentation pertaining to clinical deterioration, incidents, hospital transfers and clinical costings.

##### Inpatient facilitators

All implementation officers and nurse facilitators will be included to evaluate implementation fidelity, as they will be responsible for the implementation of HIRAID® Inpatient.

#### Randomisation

Each cluster will be randomly allocated to one of four starting dates for implementation. Randomisation will be performed by the study statistician using computer-generated numbers. Participating wards will have no influence over the allocation prior to randomisation, ensuring concealment of the allocation sequence until wards are assigned. No further changes to clusters will be made once the allocation has been finalised to minimise the risk of bias.

We are unable to randomise sites to clusters because of geographical location and clinical governance. The significant geographical distance between sites, mitigates the risk of contamination due to reduced proximity. Randomising clusters based on health service provides consistent clinical governance for study operations.

#### Blinding

Blinding investigators and staff delivering the intervention to cluster allocation is impractical. However, researchers assessing nurse-associated clinical deterioration, hospital-acquired complications, and nursing documentation will remain blinded, as well as participants not directly involved in delivering or receiving the intervention (i.e. inpatients, family of inpatients).

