#### Study Plan

##### Integration of HIRAID® Inpatient framework into hospital systems

The local electronic and paper-based documentation systems will integrate the HIRAID® Inpatient documentation templates. HIRAID® Inpatient will include a standardised template with fields and prompts for all framework elements. Hospital local factors, such as paper or electronic documentation will inform adaptation practices. Features like the product(s) used (e.g. PowerChart, Cerner electronic medical records (eMR)), automation features, and compatibility with existing tools are included. The documentation templates are designed to streamline assessment documentation, minimise duplication, alleviate administrative burdens, and reduce redundancies for hospital ward nurses. The HIRAID® Inpatient framework will be implemented alongside existing standard nursing care. No concurrent interventions are prohibited during the implementation period; however, any new initiatives or changes to routine care that may influence study outcomes will be documented.

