#### Outcomes

##### Patients with a preventable clinical deterioration (H_1_)

Rate per 1000 admissions of preventable patient deterioration calls (RRT calls) related to nursing assessment and management, observation and monitoring. RRT activation is already recorded in local databases and will be used to identify patients for medical record review, independent assessment and verification of causal factors [38]. Secondary outcome is transfer to a higher level of care (e.g. to Intensive Care Unit) (Table 3).

**Table 3 Tab3:** Summary of HIRAID® Inpatient outcome measure, data collection sources and measurement timepoints

Outcome	Outcome description	Outcome measure	Data analysis	Data source	Control (pre)	Implementation	Intervention (post)
Patient health outcomes							
Outcome 1 (H1)	Nursing-related preventable clinical deterioration	Incidence of clinical deterioration events related to nursing assessment and care	*Descriptive approach, generalised linear model (GLM) approach	Patient deterioration database, eMR records	✓	-	✓
Outcome 2 (H1)	Transfer to higher level care	Incidence of patients transferred to higher level care	*Descriptive approach, GLM approach	Patient deterioration database, eMR records	✓	-	✓
Outcome 3 (H2)	Hospital Acquired Complications (HACs) influenced by nursing care	Incidence of patient days with respiratory complication (HAC03), and/or healthcare-associated infections (HAC06)	*Descriptive approach, GLM approach	Health District data collections, Performance Planning Unit (PPU) database, eMR records	✓	-	✓
Outcome 4 (H2)	HACs influenced by nursing care–health service perspective	Incidence of hospital resource use and costs	*Descriptive approach, GLM approach	Health District data collections, PPU database, eMR records	✓	-	✓
Outcome 5 (H2)	HACs influenced by nursing care	Rate of all other HACs (not HAC03 and HAC06)	*Descriptive approach, GLM approach	Health District data collections, PPU database, eMR records	✓	-	✓
Outcome 6 (H3)	Events that cause patient harm or near miss	Incidence/proportion of adverse patient harm or near miss events	*Descriptive approach, GLM approach	Health District data collections, PPU database, eMR records	✓	-	✓
Patient and carer experience outcomes							

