##### Deteriorating patient database and electronic medical record (eMR)

Patient’s that have a rapid response call activated while an inpatient in a study ward will be identified through existing site rapid response databases. In addition to reviewing the quality of documentation using the audit tool (Supplement 1), these records will be reviewed to identify causal factors associated with the rapid response call and determine if suboptimal inpatient nursing care was a precursor, for example, unreported or delayed reporting (> 30 min) of vital sign abnormalities fulfilling hospital criteria. The instrument (Supplement 1) outlines the variables collected and incorporates the validated Human Factors Classification Framework for patient safety [38], which considers equipment, work environment, staff action and patient factors. To ensure consistent data collection, research nurses assessing clinical documentation and patient deterioration events will complete data collection on a minimum sample of 10 duplicate records to complete inter-rater reliability at commencement. Ongoing audits will maintain data collection consistency.

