##### Data de-identification and linkage

Research nurses at the study site will have access to eMR data, used to identify patients that meet study inclusion criteria and determine those patients that require medical record review and/or rapid response review. Only site researchers will have access to their identifiable site data. Once data collection is complete, all data will be imported into Excel and then integrated using the identifiers of MRN, name and age. These three identifiers are required to maximise the likelihood of correctly matching patients between datasets.

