### Methodological considerations and risks

The study requires substantial commitment from healthcare partners, including the co-design, implementation, maintenance, and evaluation of HIRAID® Inpatient. Following success in the ED, nursing management advocated for HIRAID® adoption in the hospital inpatient setting. However, input and engagement from frontline nurses must be considered. In addition to Phase 2 surveys and focus groups, an assessment of current documentation, education and orientation practices in specialty wards will be conducted to engage nursing staff and address inherent challenges unique to these diverse patient care settings.

Due to the nature of the intervention, blinding will be limited. While recipients will be blinded to cluster order, they cannot be blinded to the transition from control to intervention conditions, introducing a risk of bias in self-report measures (e.g. nurses’ perceived confidence). For non-self-reporting measures (e.g. clinical deterioration events), objective assessment and repeated measurements across baseline and post-intervention periods mitigate bias. To minimise bias, assess long-term outcomes and detect relapse effects, most outcome measures will be collected for a range of 3–12 months post-intervention.

The application of HIRAID® to a ward context poses a delivery risk. To manage this, pre-implementation diagnostics will identify potential issues, and solutions will be incorporated into the site-specific implementation plans. Implementation research nurses will escalate and manage challenges through a hospital working group and research management group.

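### The blinding claimed for assessors of preventable deterioration (H1) and nursing documentation is not supported, because the records they read will carry the HIRAID template after rollout

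*Protocol article*

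**What the plan says.** All places are in the protocol article.

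- **Blinding** concedes that investigators and staff delivering the intervention cannot be blinded, then says without qualification that "researchers assessing nurse-associated clinical deterioration, hospital-acquired complications, and nursing documentation will remain blinded".
- **Integration of HIRAID® Inpatient framework into hospital systems**: "The local electronic and paper-based documentation systems will integrate the HIRAID® Inpatient documentation templates", and "HIRAID® Inpatient will include a standardised template with fields and prompts for all framework elements".
- **Outcomes, H1** defines the outcome as "Rate per 1000 admissions of preventable patient deterioration calls (RRT calls) related to nursing assessment and management, observation and monitoring". RRT activations in local databases "will be used to identify patients for medical record review, independent assessment and verification of causal factors".
- **Deteriorating patient database and eMR** has research nurses review these records, identify causal factors and decide whether suboptimal nursing care came before the call. Late or absent reporting of abnormal vital signs is the example given. Documentation quality is audited in the same records. Consistency rests on a "minimum sample of 10 duplicate records to complete inter-rater reliability at commencement", followed by ongoing audits that are not described further.
- **Nursing documentation (H5)** takes the D-catch sample from the H1 records.
- **Methodological considerations and risks** accepts that blinding is limited and that self-report measures are at risk. For measures such as deterioration events it states that "objective assessment and repeated measurements across baseline and post-intervention periods mitigate bias".

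**The concern.** H1 does not count RRT calls. It counts calls that a reviewer attributes to preventable, nursing-related causes, so the outcome depends on a causal judgement made from the notes. The intervention changes those notes, which creates two routes to bias:

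1. A reviewer who recognises the template knows the ward's condition and may judge differently because of it.
2. The template may change what is recorded, and so change whether a sign looks unreported or reported late, even if care at the bedside is the same.

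D-catch has the same problem more directly, because the templated documentation is part of what is scored.

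If the blinding statement stands, readers of the results will credit H1 and the documentation score with a protection that the described procedures do not provide.

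**Working it through.** No stated figure is in dispute, and the sample-size table is not available in the text. The check is mainly a comparison of sections.

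**Step 1. What the assessor reads.** The H1 and H5 outcome sections and the eMR section all point to the medical record of the patient who had the RRT call.

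**Step 2. What that record shows.** The integration section puts a standardised template, with prompts for every framework element, into both paper and electronic systems. Under Study design, wards move one way, from control through a three-month transition to intervention. Either the template or the record's date therefore reveals the condition.

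**Step 3. Whether anything described hides it.** The article does not mention redaction, date masking, random-order review or central review away from the sites. The independent assessment named for H1 concerns who judges, not what they can see. Not knowing the randomised order of clusters does not help either, because the condition at the time of the call is what matters.

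**Step 4. Whether the reliability check would reveal a shift.** Ten duplicates at commencement most naturally fall before templated records exist, since every cluster starts in control, although the article does not name the phase. The ongoing audits are not said to duplicate intervention records or compare phases. The number is also small. Using SE = √[po(1 − po)/n] / (1 − pe), with an assumed kappa of 0.8:

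| Prevalence judged preventable (assumed) | n | po | pe | SE | 95% interval |
|---|---|---|---|---|---|
| 0.5 | 10 | 0.90 | 0.50 | 0.19 | 0.43 to 1.00 |
| 0.3 | 10 | 0.916 | 0.58 | 0.21 | 0.39 to 1.00 |
| 0.3 | 100 | 0.916 | 0.58 | 0.066 | 0.67 to 0.93 |

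The formula is a large-sample one, so the n = 10 rows are rough, and their upper limits are cut at 1. Kappa measures agreement between reviewers, not a shift between phases. More duplicates help with the present concern only if they come from both phases.

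**Step 5. How large a shift would matter (assumed values only).** With no false positives, observed rate ratio = true rate ratio × (probability that a truly preventable call is labelled so after rollout ÷ the same probability before).

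- True ratio 1.00, 10% fewer labels: 1.00 × 0.90 = 0.90, half of the 20% target.
- True ratio 1.00, 20% fewer labels: 1.00 × 0.80 = 0.80, the whole target. For example, 24 instead of 30 calls per 100 judged preventable is (30 − 24)/30 = 20%.
- True ratio 0.80, 25% more labels: 0.80 × 1.25 = 1.00, so a real effect disappears.

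The documents give neither the baseline proportion nor any labelling shift.

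**The case against.** The strongest reply is that the article says assessors are blinded and does not say that they see the template. A condensed article may leave the masking procedure to the full protocol or to the review instrument in Supplement 1. The eligibility section also speaks of collecting de-identified patient data, so review of prepared extracts is possible. This stands in part: a reader might infer that the assessors are unblinded as a matter of fact, and the article does not establish that. But removing patient identifiers does not remove a template. The point is also not about omitted detail, because the article makes a positive claim that the procedures it describes do not support.

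Other stronger readings also go beyond the text:

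- **That site nurses or implementation nurses judge H1.** The article states that "Only site researchers will have access to their identifiable site data" and gives site research nurses a role in finding the records to review. It does not say who adjudicates.
- **That the bias favours the intervention.** Fuller notes could equally expose more missed signs and raise the count judged preventable.
- **That H1 has no unadjudicated support.** Transfer to higher-level care is a planned H1 secondary outcome and needs no preventability judgement. What is not listed is an all-cause RRT rate.
- **That the article dismisses bias.** It claims only mitigation, in a paragraph that opens by admitting limited blinding.
- **That hospital-acquired complications are affected in the same way.** They come largely from routine data collections and are not part of this point.

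**Conclusion.** The concern holds as an unsupported blinding claim, not as proof of unblinded assessment. On the procedures described, the control or intervention condition is likely to be visible when H1 preventability and D-catch are judged. Calling the assessment objective does not remove the problem, because attributing cause is a judgement. The specified duplicate review is not designed to detect a difference between phases.

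Neither the size nor the direction of any bias can be derived from the documents. The illustrations show only that a relative labelling change of 20% to 25% would be enough to create or cancel the planned effect. They rest on assumed values and on no false-positive labels. The conclusion would change if the full protocol or Supplement 1 describes masking that removes template format and dates. For D-catch such masking is hard to achieve at all.

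**What to change.** 1. **Blinding section:** withdraw or qualify the claim for H1 and documentation. If masking is planned, state who is masked, to what and how. For D-catch, acknowledge that the template is part of what is scored.
2. **Methodological considerations and risks:** list likely visibility of the condition during record review as a limitation, with direction unknown.
3. **Outcomes, H1:** prespecify all-cause RRT calls per 1000 admissions as an unadjudicated companion, beside transfer to higher-level care and analysed with the same model as H1. It is not a clean check. Better escalation may itself raise all-cause calls, and non-preventable calls dilute any effect.
4. **Duplicate review:** draw the records from both phases and all four clusters, and report agreement by phase.
5. **Record review:** review control and intervention records in random order, with dates and template headings masked where the extract allows.

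Items 1 and 2 are wording. Item 3 needs no new data, because activations are already held in local databases. Items 4 and 5 cost some masking work and extra duplicate reviews by existing reviewers, and records must be held so that phases can be mixed. Recruitment is scheduled to begin on 1 July 2026, so these changes should be settled before then.
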